## Criteria for breaking the code

| Laboratory Parameter | Cut-off Point |
| --- | --- |
| Hb | < 7 g % |
| TLC | < 3000 |
| Platelet Count | < 1 lakhs |
| SGOT | > 50 |
| Creatinine | > 2 |

In case of abnormal blood counts, the following guidelines should be followed:

| Laboratory Parameter | Level | Action |
| --- | --- | --- |
| Total WBC | < 3 X 109/l | Break Code / Continue steroids |
| Absolute Neutrophil Count | < 1.0 X 109 /l | Break Code / Continue steroids |
| Absolute Neutrophil Count | < 0.5 X 109 /l | **If febrile**, start **antibiotic** and look for source of infection  As per guidelines in Field Manual |
| Hb | < 7.0 g/dl | Break Code / Continue steroids |
| Hb | Fall > 3 g/dl from baseline | **Break Code / Continue steroids** |
| Platelets | < 100000 | **Break Code/ Continue steroids** |
| Serum Creatinine | > 50 % above baseline | **Break Code / Continue steroids** |
| SGOT | > 2 X upper limit of normal | **Break Code / Continue steroids** |

## Patient outcome measures

### Primary outcomes

1. **Recovery of nerve function**

- Absolute improvement in nerve function as measured by Voluntary Muscle testing (one point improvement in VMT score) and Sensory testing (two point improvement in ST score) using standard methods as defined in the field manual.

1. **Recurrence of neuritis during or after treatment**

- Recurrence of neuritis is defined as a new nerve function impairment presenting in the form of a decrease in VMT score by one point and an ST score by more than 2 points either during the study period or during the follow up period and present for two consecutive testings.

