#### Determining the eligibility for the study

All patients with a diagnosis of leprosy (whether paucibacillary or multibacillary) and evidence of recent onset neuritis or recurrent skin lesions in type 1 reactions will be included in the study as long as he/she satisfies the inclusion criteria and does not have any absolute exclusion criteria listed in table 1. For the purpose of this study neuritis will be defined as: -

- Spontaneous nerve pain, paraesthesia or tenderness (or)
- New sensory or motor impairment of recent onset detected by voluntary muscle testing and sensory testing (or)
- Mixed sensory and motor signs.
  - The MDT status (past or current) of the patient does not affect eligibility provided they have recent neuritis or recurrent reactional skin lesions.
- Patients who are already on steroids (started within the past one month) will be included if they present with new nerve damage or fresh evidence of neuritis while on treatment with steroids.

The local MO decides whether the patient can be included in the study.

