#### Inclusion Criteria:

Patients with acute (< 6 months) neuritis with or without accompanying type 1 reaction or recurrent reactional skin lesions without neuritis.

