***Flow Chart for Recruitment***

NFI

Recurrent reactional skin lesions

Informed

Consent

(Form 1)

No

yes

Full Blood Count

Exclude

Hb < 7 gm

TLC < 3000

Platelets < 1 lac

No

Register for trial

(Form 2)

Randomize

Arm 1

Arm 2

Arm 3

Arm 4

Yes

Age < 15 yrs

Wt < 30kgs

Pregnancy

On treatment for TB

H/O Jaundice in last 3 m

Pre-existing bone marrow disease

Hepatic Dysfunction

Known HIV positive

Unable to come regularly

Form E

Yes

Yes

No

NFI < 6 months

Or recurrent reactional skin lesions

Form 3.0

Baseline history

& Examination

Lab tests

Randomised Study Patient

Form 4.0

Baseline ST

Form 5.0

Baseline VMT

Form 6.0

Baseline Lab Investigations

##

Allot 4 weeks treatment box

Follow up Visit

Lab tests

Form 6.1

Clinical

Form 3.1

ST

Form 4.1

VMT

Form 5.1

Serious

Adverse effects

Hb < 7.0

TLC < 3000

Platelet

Count < 1 lakh

Break

Code

Worsening

Improvement

Add steroids

Continue in study

Normal

SGOT < 50

Creatinine < 2.0

Treat accordingly

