## Statistical analysis

The primary analysis will be a comparison of azathioprine plus prednisolone with prednisolone alone for achieving the primary outcome following the “intention to treat” principle. Intention to treat analysis will also be performed for the secondary outcomes.

Analysis of endpoints, comparing time to event in the four arms will be performed.

Pre-planned sub group analysis will be performed for the following subgroups (male, female; MB, PB; previous T1R, new T1R).

A secondary on treatment analysis will be performed to explore the requirement of additional steroids as well as adverse effects with these drugs.

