### *Definitions:*

### *Neuritis*: A leprosy patient is diagnosed as having neuritis when he/she has any of the following:

- Spontaneous nerve pain, paraesthesia or tenderness (or)
- New sensory or motor impairment of recent onset detected by voluntary muscle testing and sensory testing (or)
- Mixed sensory and motor signs

*Acute Neuritis*: For neuritis to be acute it has to have appeared within the last six months (defined either by previous testing or patients history of new sensory or motor loss)

*Type1Reaction* (T1R) is defined as the development of an acute or subacute inflammation affecting the skin and / or nerves occurring in leprosy, due to a hypersensitivity to *M.leprae* antigens, resulting in a change in the appearance of skin lesions and / or nerve damage and disability.

A T1R is diagnosed when a patient has erythema and edema of skin lesions. There may be accompanying neuritis and edema of the hands, feet and face. The skin signs are obligatory; the nerve and general signs optional.

*Acute T1R* is defined as the presence of erythematous and raised skin lesions with or without evidence of neuritis of less than 6 months duration prior to presentation.

*Recurrent reactional skin lesions* are defined as newly erythematous lesions that have either developed off steroids or whilst on steroids.

*Silent Neuropathy (SN)*

A patient is defined as having silent neuropathy when he/she has sensory and/or motor impairment of recent onset (< 6 months duration) in an area innervated by one or more nerve without signs of a reaction (RR or ENL) or nerve pain and with or without tenderness.

*Sensory Impairment:* A patient is diagnosed as having sensory impairment in any of the following situations: the monofilament threshold was increased from the normal threshold (2gm/purple for the hand and 10gm/orange for the foot) by three or more levels (filaments) on any site, OR two levels on one site AND at least one level on another site, or one level on three or more sites for one nerve.

*Motor Impairment:* A patient will be diagnosed as having motor impairment if the VMT score for any muscle is four or less on the 0-5 (modified) MRC scale.

*Worsening of skin lesions:* is defined as occurrence of a fresh episode of acute skin inflammation with or without edema while enrolled in the study.

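### Primary outcome 1 needs a gain in nerve function but sets no baseline condition, while the trial enrols patients who may have no impairment to recover from

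*Protocol*

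**What the plan says.** **Outcome.** Under Primary outcomes, item 1 is absolute improvement on voluntary muscle testing ("one point improvement in VMT score) and Sensory testing (two point improvement in ST score"). No starting level is required.

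**Who enters.** The Inclusion Criteria read "Patients with acute (< 6 months) neuritis with or without accompanying type 1 reaction or recurrent reactional skin lesions without neuritis". The section on determining eligibility, and the Definitions, list alternative signs of neuritis, of which the first is "Spontaneous nerve pain, paraesthesia or tenderness (or". Symptoms without measured loss therefore qualify. The section on identifying eligible patients and the Flow Chart for Recruitment are narrower on this point. They ask for nerve function impairment (NFI, under 6 months in the flow chart) and then give the alternative "Or recurrent reactional skin lesions".

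**Ceiling.** The Definitions diagnose motor impairment "if the VMT score for any muscle is four or less on the 0-5 (modified) MRC scale".

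**Analysis.** The Statistical analysis section says "The primary analysis will be a comparison of azathioprine plus prednisolone with prednisolone alone for achieving the primary outcome following the" intention-to-treat principle. It does not limit the recovery analysis to impaired patients. The listed subgroups are "male, female; MB, PB; previous T1R, new T1R", none of them by baseline impairment. Resolution of skin lesions, the outcome that suits skin-only patients, is secondary.

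**The concern.** Eligibility and the first primary outcome do not describe the same patients. A patient who enters with a skin reaction and full muscle strength, or with nerve pain only, has no VMT point to gain. If every randomised patient is in the denominator, such patients add non-recoveries to all four arms. The absolute difference shrinks in proportion to their share, and the comparison loses power on an outcome that they could not inform.

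The wording adds a second problem. If one patient must gain on both VMT and ST, someone with purely motor or purely sensory loss cannot qualify either. The Definitions join the two tests with *or* when they define worsening of acute neuritis, while both primary outcomes join them with *and*. Who counts as a responder depends on which is meant.

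**Working it through.** **1. Side by side.** An unimpaired muscle scores 5, the top of the scale, so no further VMT point is available. Skin-only patients enter on every version of the entry rule. Pain-only patients enter under the eligibility text and the Definitions, but not under the flow chart. The ceiling therefore applies to some enrolled patients whichever entry rule is followed.

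**2. The plan's own figure.** The Sample size section uses SD 2 and d = 1: 2 × [(1.96 + 0.842) × 2 / 1]² = 62.8, so 63 per group. This reproduces. It is based on a combined skin, sensory and motor score, not on recovery as defined in item 1, and contains no allowance for patients who cannot reach that outcome.

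**3. Illustration of the dilution.** Inputs:
- Group sizes: 63 controls and 3 × 63 = 189 for the three azathioprine arms pooled.
- Control recovery among impaired patients: 70%, the top of the 60% to 70% cited in the Background.
- Azathioprine: 70% × 1.25 = 87.5%. This borrows the 25% improvement that the Sample size section applies to the combined score, and is an assumption here.
- Share f unable to respond: not in the Protocol; 10%, 20% and 40% are assumed.

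With everyone analysed, both rates are multiplied by (1 − f). With the analysis restricted to impaired patients, the rates stay and both group sizes are multiplied by (1 − f).

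Power = Φ[(Δ − 1.96·s0)/s1], where s0 is the standard error of the difference under the pooled rate and s1 the standard error under the separate rates.

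- At f = 0: Δ = 0.175, s0 = 0.0545, s1 = 0.0625, so Φ(1.09) = 86%.
- At f = 20%, everyone analysed: Δ = 0.70 − 0.56 = 0.14, s0 = 0.0687, s1 = 0.0709, so Φ(0.08) = 53%.
- At f = 20%, restricted (50.4 vs 151.2): Δ = 0.175, s0 = 0.0609, s1 = 0.0699, so Φ(0.80) = 79%.

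| f | Rates, everyone analysed | Power, everyone | Power, impaired only |
|---|---|---|---|
| 0 | 70.0% vs 87.5% | 86% | 86% |
| 10% | 63.0% vs 78.75% | 69% | 83% |
| 20% | 56.0% vs 70.0% | 53% | 79% |
| 40% | 42.0% vs 52.5% | 30% | 68% |

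**4. Sensitivity.** With 60% vs 75% (again × 1.25) and f = 20%, power is 38% for everyone and 53% restricted. With separate rather than pooled variance, the 70% vs 87.5% case gives 80% at f = 0; at f = 20% it gives 51% for everyone and 71% restricted. The levels move, but the ordering does not.

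**The case against.** **Failure status is inferred.** The Protocol never says that unimpaired patients count as failures. The word *recovery* can be taken to presuppose a deficit, and an analysis plan not shown here could define the denominator. This stands as a limit on wording. However, the Protocol defines the outcome without a baseline condition and names intention to treat without restriction, and followed as written that includes these patients.

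**Not all of them are at the ceiling.** *Without neuritis* may mean no recent neuritis, so some skin-only patients may have older loss that can improve. ST scoring is in the field manual, which is not shown, so only the VMT ceiling can be verified. Both points stand.

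**The word *and* may only list two instruments,** each with its own threshold. That is a fair reading. The text is ambiguous; it does not settle that both gains are required.

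**Enrolling skin-reaction patients is deliberate.** The Study Aims include them, and they can contribute to recurrence of neuritis and to both secondary outcomes. That is right, and the point is confined to primary outcome 1.

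**Stronger readings that the Protocol does not support.** A reader might infer that the table shows power lost from the planned 80%. It does not, because the trial was sized on a different score to which skin-only patients can contribute. A reader might infer that a chance imbalance in the unimpaired share would bias the result, but that is random error already covered by the significance level. A reader might also infer that unconfirmed gains make many recoveries spurious. The Protocol gives no measurement error rate and does not say that a gain at any single visit is enough, so no such rate can be derived.

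**Conclusion.** The mismatch holds and should be corrected, because it decides who can be a responder on the first primary outcome. As written, the plan puts into the recovery comparison patients with no VMT point to gain, and leaves open whether one or both gains are needed. The direction is certain for patients with every muscle at 5 if both gains are required. If either gain suffices, it also depends on the ST scoring, which cannot be checked here.

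The size is unknown, because f and the recovery rates are assumptions. In every scenario calculated, the analysis restricted to impaired patients has more power than the analysis of everyone, although it uses fewer patients.

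**What to change.** In Primary outcomes and Statistical analysis, define the recovery analysis set as all randomised patients with motor or sensory impairment at baseline, by the Protocol's own Definitions and Forms 4.0 and 5.0, compared by randomised arm. Count as recovered a VMT gain of at least 1 in those with motor impairment, or an ST gain of at least 2 in those with sensory impairment. State that these forms are completed before the first dose, so that membership cannot depend on treatment and the randomised comparison is kept.

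Keep every randomised patient in the recurrence and skin analyses. Optionally, require the gain on two consecutive testings, as recurrence already does. Reconcile the eligibility text and Definitions with the flow chart and the section on identifying patients, so that it is clear whether pain-only neuritis qualifies.

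**Cost.** No new data are needed. The denominator and precision for this outcome fall: having 63 impaired patients per arm takes 63/(1 − f) evaluable patients, which is 70, 79 and 105 at f = 10%, 20% and 40%. It also changes the definition of a primary endpoint, so it must be fixed and documented before unblinding.

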## Introduction:

## Study Aims

The primary aim of this study is to compare the neurological outcomes in patients with type 1 reactions and recurrent type I reactions in skin lesions, when they are treated with either Azathioprine in addition to a 20-week course of prednisolone or prednisolone alone.

The objectives of the study are: -

1. Improves dermatological outcomes in Type 1 reactions.

2. Improves neurological outcomes in Type 1 reactions and neuritis

3. Reduces the recurrence rate (i.e. requirement for further treatment with steroids) in patients with T1R and neuritis.

4. To compare the effectiveness of different duration of treatment with Azathioprine in T1R and neuritis.

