## Patient Follow up: Management of Complications

1. If the neuritis / type 1 reaction worsens (as per defined criteria of VMT and sensory testing) while the steroid is being tapered, then the dose of Prednisolone will be STEPPED UP to the preceding dose. After 20 weeks when Prednisolone has been stopped, if worsening occurs, the patient will be restarted at 40 mg of Prednisolone.
2. If the patient develops medical complications like leucopenia, jaundice or anemia it is imperative that this is investigated as per the protocol to determine the etiology. It should not be assumed that complications are caused by the trial drugs.
3. In case the patient is detected to have potential adverse effects of the drug(s) by lab investigations as listed in the flow diagram, then code will be broken by study coordinator
4. In case the patient develops clinical symptoms and signs suggestive of a severe adverse effect, such as systemic sepsis or gastro intestinal bleed then the patient will be admitted into the corresponding hospital and treated accordingly. The Study Coordinator will be contacted and the case reviewed. The Study coordinator will determine whether to break the code or continue the trial after symptomatic treatment.
5. In case a patient gets pregnant while enrolled in the study, she can be reassured that Azathioprine is highly unlikely to affect the fetus and continued in the study. However she may discontinue if she so wishes, in which case her nerve function assessments will be continued as per schedule.
6. In case of infections such as Tuberculosis, patient will be started on Anti Tuberculosis Treatment (ATT) after relevant investigations and continued in the study.

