## Sample size

The sample size calculation was based on the expected improvements in the combined scores (skin, sensory & motor) that the addition of azathioprine to prednisolone would produce. It was calculated that the addition of azathioprine would produce a 25% improvement in the combined scores. This would be a score of 4 allowing for an alpha of 0.05 and beta of 0.80, the minimum sample size is calculated as follows:

n=2x[(Zα +Z1-β)xSD)/ d]2 =2x[(1.96+0.842))x2)/1]2 = 63 per group.

We assumed a ‘lost to follow up’ rate of 15%, and dropout rate due to adverse reactions of 10 %,so minimum of 78 patients would be required per arm, and a total of 312.

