*Worsening of Acute Neuritis*: is defined as evidence of nerve function impairment as evidenced by at least a single point decrease in VMT score or a two-point decrease in ST score from baseline, in two consecutive testings.

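### Recurrence of neuritis, a primary outcome, is worded to need both motor and sensory loss, whereas the worsening rule evidently behind added steroids needs only one

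*Protocol*

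**What the plan says.** Protocol, Primary outcomes, item 2, defines recurrence of neuritis as new nerve function impairment shown by "a decrease in VMT score by one point and an ST score by more than 2 points". The loss may arise at any time on study or in follow-up, and it must be seen at two testings in a row. The section does not say from what level the fall is measured.

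Protocol, Definitions, describes worsening of acute neuritis as "at least a single point decrease in VMT score or a two-point decrease in ST score from baseline, in two consecutive testings".

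Protocol, Management of Complications, item 1, covers the case where neuritis or type 1 reaction "worsens (as per defined criteria of VMT and sensory testing) while the steroid is being tapered". Prednisolone is then stepped up, or restarted if the worsening comes after week 20. The section does not name the definition it relies on. The Definitions entry for acute neuritis is the only worsening criterion in the protocol that is expressed in VMT and ST points.

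Two other places bear on the point. Study Aims, objective 3, reads "Reduces the recurrence rate (i.e. requirement for further treatment with steroids) in patients with T1R and neuritis". The neuritis definition, given under eligibility and again under Definitions, accepts sensory or motor impairment alone.

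**The concern.** The recurrence outcome and the worsening definition use the same two instruments and the same confirmation rule, but they differ in three ways: the connector (both against either), the ST threshold (more than two points against two), and the reference level (unstated against baseline).

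A patient can enter with motor-only neuritis, recover, relapse in the same way, be given more prednisolone under the protocol, and still count as recurrence-free. Objective 3 treats the need for further steroids as the meaning of recurrence, so for that patient the outcome contradicts the objective it should serve. Additional steroid need appears in neither the primary nor the secondary outcome list. The Statistical analysis section mentions it only within a secondary on-treatment analysis.

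**Working it through.** **Step 1. Set the rules side by side.**

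| Element | Recurrence (primary outcome 2) | Worsening of acute neuritis (Definitions) |
|---|---|---|
| Motor | VMT fall of one point | VMT fall of at least one point |
| Connector | and | or |
| Sensory | ST fall of more than 2 | ST fall of 2 |
| Reference level | not stated | baseline |
| Confirmation | two consecutive testings | two consecutive testings |

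**Step 2. Apply both rules to each pattern of loss.** Falls are taken from baseline and confirmed at two consecutive testings. The one-point and two-point criteria are read as at least that much.

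| Pattern | Meets worsening (steroids added) | Counts as recurrence |
|---|---|---|
| VMT −1, ST 0 | yes | no |
| VMT 0, ST −3 or any larger fall | yes | no |
| VMT −1, ST exactly −2 | yes | no |
| VMT −1, ST −3 | yes | yes |

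At a common reference level, every loss that meets the recurrence rule also meets the worsening rule, but not the reverse. The literal outcome can therefore only lose events relative to an either-test rule.

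**Step 3. Reference level.** Take a patient whose VMT goes from 2 at baseline to 5 and back to 3. Against baseline the change is 3 − 2 = +1, which is not worsening. Against the best score it is 3 − 5 = −2, a fall. The recurrence outcome does not say which applies, so assessors could score the motor part of the same record differently.

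**Step 4. The plan's own figure.** The Sample size section uses SD 2 and difference 1, "allowing for an alpha of 0.05 and beta of 0.80" (the 0.842 in its formula corresponds to 80% power). This gives 2 × [(1.96 + 0.842) × 2 / 1]² = 62.81, rounded up to 63 per group, so the figure reproduces. It rests on a combined skin, sensory and motor score, so it neither depends on the recurrence definition nor supplies a recurrence rate.

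**Step 5. Illustration only.** Assumptions:
- 63 per arm, one azathioprine arm against control, two-sided 0.05.
- Either-test relapse in control of 50% or 30%. The Background reports that 50% needed further steroids on a 12-week regimen in an earlier trial, which is not a recurrence rate for this 20-week course. The 30% is simply a lower value.
- A 40% relative reduction, and a share s of relapses that meet the both-tests rule, equal in the two arms. Neither is in the protocol.

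Power = Φ{[|p₁ − p₂| − 1.96√(2p̄(1 − p̄)/n)] / √([p₁(1 − p₁) + p₂(1 − p₂)]/n)}, where p̄ = (p₁ + p₂)/2.

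- Either-test rule, 50% v 30%: (0.20 − 1.96 × 0.0873)/0.0854 = 0.34, power 63%.
- Both-tests rule, s = 20%, 10% v 6%: (0.04 − 1.96 × 0.0483)/0.0482 = −1.14, power 13%.

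| Control relapse (either test) | Either rule | Both, s = 20% | s = 40% | s = 60% | s = 80% |
|---|---|---|---|---|---|
| 50% | 63% | 13% | 23% | 35% | 49% |
| 30% | 35% | 9% | 15% | 21% | 28% |

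The spread across s shows that the loss depends on a quantity the protocol does not give.

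**The case against.** The strongest reply is that the word joining the two tests may only list one threshold per instrument. The recovery outcome, item 1 of the same section, uses the same construction, and the neuritis definition lets either modality qualify. If an either-test rule was intended, no treated relapse is lost through the connector. That is a fair reading of intent. It still leaves a primary outcome with two readings, and it does not explain the different ST threshold or the missing reference level. The field manual is cited in that section for testing methods under the recovery item, not for the recurrence definition.

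A second reply is that a sensitive treatment trigger can properly sit beside a stricter efficacy endpoint. In general it can. Here, though, objective 3 equates recurrence with further steroid treatment, so the protocol does not present the stricter rule as a deliberate choice.

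The link from the steroid rule to the worsening definition is inferred, not stated. It is the natural inference, since no other VMT and ST criterion for worsening is given.

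A reader might also infer that the protocol holds three rival definitions of recurrence. It does not: only the outcome section defines recurrence. The Definitions entry concerns worsening, and objective 3 is a gloss that also covers type 1 reaction.

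**Conclusion.** The point holds as a contradiction in wording that affects one of the two primary outcomes. Read literally, confirmed single-modality relapses, and mixed relapses with an ST fall of exactly two points, are treated with steroids and scored as no recurrence. The direction is certain, because the both-tests rule can only remove events. The size is unknown, because the protocol gives neither a recurrence rate nor a motor, sensory and mixed split.

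Four stronger readings are tempting but not supported:
- That most relapses are missed. This needs the split that is absent.
- That the comparison is biased toward no difference. If the same share of relapses is missed in each arm, the risk ratio is unchanged (0.30/0.50 = 0.06/0.10 = 0.6) and the loss is in events and power. A rescue effect that differs by arm is plausible but cannot be sized from the document.
- That a rescued patient will hardly ever go on to meet the both-tests rule. The Background says up to 30% may not improve on prednisolone, so some could progress to both.
- That the low power in the illustration is due to the definition alone. Under the same assumptions the either-test rule gives only 63% or 35%, and the trial was not sized on recurrence.

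**What to change.** In Primary outcomes, item 2, define recurrence as a fall of at least one VMT point or at least two ST points, present at two consecutive testings. State one explicit reference level, chosen before unblinding. Which level to use is for the trial team to decide; what matters is that it is fixed and applied to all arms.

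Report the need for additional prednisolone as a separate intention-to-treat outcome serving objective 3. It should stay apart from recurrence of neuritis because the steroid rule also responds to worsening type 1 reaction, so the two will not coincide.

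Reconcile the recurrence outcome, the worsening definition and Management of Complications, item 1, so that each says which criterion it uses. The clinical trigger for steroids remains with the investigators, and nothing here proposes a change to it.

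The cost is an amendment in wording. VMT and ST are already recorded at every follow-up visit, so no new assessments are needed. The downside is somewhat more measurement noise from changes on a single test, which the existing requirement for two consecutive testings limits.
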